### **Pre-clinical evidence that fluid resuscitation may be harmful in septic shock**

A pre-clinical trial induced experimental septic shock by IV injection of lipopolysaccharide (LPS) in an ovine model, with subsequent randomisation to fluid resuscitation with normal saline (40 ml/kg), or no fluid resuscitation. This demonstrated that an initial fluid bolus is associated with (a) myocardial damage with raised troponin levels; (b) EG damage and raised ANP levels; and (c) increased vasopressor requirements [20]. These

findings challenge the current paradigm and are consistent with the results of the two African trials. This further supports the concept that fluid boluses are not only ineffective for treating hypotension, but may actually exacerbate shock in the setting of sepsis.

### Support for a volume-sparing/early vasopressor approach

Accumulating evidence from observational studies, experimental models, and randomised trials in resource-poor countries challenge the standard approach to early fluid volume resuscitation recommended by the SSC. While there is currently no high-quality evidence to guide practice in the ED in industrialised countries, the question has been addressed in ICU populations. In a meta-analysis of 11 clinical trials, Silversides *et al* found a fluid restrictive approach in ICU was associated with increased ventilator-free days and reduced ICU length of stay [21].

[figure not shown]

**Figure 2. Clinical outcomes among 151 ICU patients randomised to either fluid restriction or usual care fluid resuscitation for septic shock in the CLASSIC trial; median (IQR) fluid volume in first 5 days post-randomisation, 0.5(0-2.5) L vs 2.0(1.0-4.1) L [22].**

Hjortrup *et al* published a pilot clinical trial of restricted fluid boluses versus usual care among 151 ICU patients with septic shock in Denmark and Finland (Figure 2) [22]. A lower resuscitation fluid volume administered during the ICU stay coincided with a significant reduction in renal injury and non-significant reductions in ischaemic events and mortality. Over 4 L of fluid was administered prior to randomisation. While none of these trials can inform resuscitation practices in the ED, they have prompted critical re-evaluation of the role of fluids in septic shock resuscitation globally.

A recently completed systematic review and meta-analysis of 621 patients with sepsis randomised to a fluid restricted versus usual care fluid regimen in 9 clinical trials between 2015 and 2018 was conducted[23]. The pooled OR for mortality showed no difference between the two regimens but the treatment effect estimate favoured fluid restriction (0.87 [95% CI 0.69, 1.10]).

Li *et al* published a systematic review and meta-analysis of studies comparing early versus later initiation of vasopressors in patients with septic shock [24]. In 5 studies involving 929 patients the early vasopressor strategy was associated with a lower volume of fluid in the first 6 hours, a shorter time to achieve target MAP and lower short term mortality. There was however substantial heterogeneity, and only 2 of the 5 studies were clinical trials.

### **Is a liberal IV fluid approach of benefit? Lessons from perioperative medicine**

The multicentre Restrictive Liberal Fluid Therapy in Major Abdominal Surgery (RELIEF) trial randomised 3000 high-risk patients (the majority from Australia and New Zealand) undergoing elective major abdominal surgery to a liberal *versus* restricted perioperative fluid management regimen [25]. Although there was no difference in the primary outcome of 1-year disability-free survival, contrary to expectations based on previous smaller trials, the rates of surgical site infections and acute kidney injury (including need for dialysis) were higher in the restricted fluid group. Translation to patients with septic shock in the ED is not possible. Nevertheless, this demonstrates the importance of undertaking high-quality, large, randomised, multicentre clinical trials where equipoise exists [26].

### **Relationship of ARISE FLUIDS with current international trials**

The Crystalloid Liberal versus Vasopressors Early (CLOVERS) trial is currently addressing the effect of these two resuscitation strategies on mortality among ED patients with suspected sepsis in the USA <https://clinicaltrials.gov/ct2/show/NCT03434028>. Resuscitation practices in the USA typically involve a larger initial fluid volume compared to Australia and New Zealand [27]. We are also interested in the effect on the *quality of survival* and have chosen outcome measures appropriate for this objective. Thus, differences in population characteristics, usual resuscitation practice and outcomes of interest necessitate a stand-alone trial.

The European *Conservative versus Liberal Approach to Fluid Therapy of Septic Shock in Intensive Care (CLASSIC)* trial <https://clinicaltrials.gov/ct2/show/NCT03668236> is assessing the effect of a fluid restricted resuscitation regimen upon 90-day mortality among patients admitted to the ICU following initial resuscitation. The trial does not therefore address the question of the optimal approach to initial resuscitation.

The principal investigators of the CLOVERS and CLASSIC trials are protocol advisors to the ARISE FLUIDS trial. We aim to harmonise relevant data points and outcome measures to facilitate a future individual patient data meta-analysis (IPDMA) akin to that which was undertaken for the trilogy of early goal-directed therapy trials [28].

### **Preliminary data and feasibility**

We recently completed an observational study of initial sepsis resuscitation practices in 70 hospitals in Australia and New Zealand (n=591) [29]. Among those with septic shock (n=82), in-hospital mortality was 8% (95% CI 3-

15%). A median volume of 4.8 L (IQR 3.9-6.2 L) was given in the first 24 hours. The fluid volume prior to commencing vasopressors was 2 L (IQR 1.2-3.0 L). Even accounting for confounders such as source of infection, age and comorbidity, this study demonstrates considerable variation in usual care and scope to undertake a trial comparing a smaller initial volume of fluid combined with earlier vasopressor use to a larger initial volume and later vasopressor administration to restore systemic arterial blood pressure in patients with early septic shock.

A vasopressor infusion conventionally requires insertion of a central venous catheter (CVC). In the ARISE trial, 40% of patients initially commenced vasopressors via a peripheral IV catheter prior to CVC insertion [30], particularly for sicker patients with shock [31]. We performed a systematic review which verified the safety of this approach [32]. Accordingly, initial peripheral vasopressor administration in our trial will facilitate earlier introduction and avoid unnecessary CVC insertion where vasopressors are required for only a short period of time.

Finally, we have completed a multicentre, pilot, randomised, clinical trial in patients presenting to ED with sepsis-induced hypotension; the Restricted Fluid Resuscitation in Sepsis associated Hypotension (REFRESH) trial [33]. Patients with sepsis and hypotension persisting after 1000 mls IV fluid, were randomised to a further fluid bolus (standard volume) or to restricted fluids plus vasopressors if required (n=94). The mean fluid volume administered pre-randomisation in the restricted and standard arms was  $1.3 \pm 0.3$  L and  $1.4 \pm 0.4$  L respectively. The mean total volume in the first 6 hours (including pre-randomisation) was  $2.3 \pm 0.9$  L ( $31 \pm 13$  ml/kg) in the restricted arm versus  $3.1 \pm 1.1$  L ( $46 \pm 20$  ml/kg) in the standard volume arm,  $p=0.0001$ . Rates of vasopressor use were similar, but median duration of vasopressor support was 20 (IQR 9-43) hours and 33 (IQR 13-50) hours respectively. With the appropriate personnel and financial support for the ARISE FLUIDS trial we expect to be able to reliably deliver the intervention and achieve clinically important separation between the comparator groups in the acute care setting.

### **Validity of trial primary outcome**

Septic shock is associated with significant mortality and reduced quality of life in survivors. The primary outcome of days alive and out of hospital to day 90 (DAOH-D90) is a patient-centred outcome measure that will capture both death and morbidity. DAOH has been validated in other settings where mortality alone is insufficient to capture the burden of disease, particularly the longer term functional outcome sequelae [34, 35]. The choice of DAOH-D90 was informed by extensive consumer consultation with time spent out of hospital and at home considered to be an important outcome. DAOH is readily quantifiable and is currently being used as an outcome measure in another critical care trial [36]. A between group difference of 7 days in DAOH-D90 was informed by data from the ARISE randomised clinical trial and the ARISE FLUIDS observational study and is considered to be biologically plausible, clinically meaningful and important to sepsis survivors. In addition to capturing the overall burden of disease both in hospital and after discharge, a 7-day reduction in DAOH-D90 will have significant resource and cost implications.

## **Significance**

On the basis of the existing evidence, there is equipoise about the effect of a fluid-restricted and early vasopressor strategy compared to a more liberal fluids and later introduction of vasopressors strategy on sepsis mortality and on longer term functional outcome among survivors. In addition, the organisational and resource implications for acute health systems of these approaches are unknown. The ARISE FLUIDS trial will address an important gap in the evidence base regarding the early haemodynamic management of patients with septic shock, provide clear guidance for bedside clinicians and optimise important patient-centred outcomes.

If it can be demonstrated that a volume-sparing approach increases the number of days-alive out of hospital, the potential impact on global resource use in the healthcare system will be substantial. We will undertake a detailed economic evaluation and follow patients up to assess their functional outcome at 12 months, a time frame which is relevant for consumers and supported by literature. The collaboration between researchers in the ANZICS CTG and the ACEM CTN will be further strengthened. Harmonisation with collaborative trials overseas will place Australia and New Zealand in the vanguard of a worldwide research effort to reduce the human and economic burdens of this World Health Organisation Global Health Priority disease.

## 7. OBJECTIVES

### 7.1 Aim

The primary aim of the study is to compare the effect of a strategy of restricted IV fluid volume and earlier introduction of vasopressors (vasopressors) to a strategy which involves a larger initial IV fluid volume and later introduction of vasopressors if required (fluids) to restore systemic arterial blood pressure, for haemodynamic resuscitation of patients with early septic shock presenting to the ED in Australian and New Zealand hospitals.

### 7.2 Hypothesis

We hypothesise that a restricted intravenous fluid volume and earlier introduction of vasopressors approach, compared to a larger initial intravenous fluid volume and later introduction of vasopressors approach to restore systemic arterial blood pressure, will increase the number of days alive and out of hospital at day 90 in patients presenting to the ED with early septic shock.

## 8. STUDY OUTCOME MEASURES

### 8.1 Primary outcome

The primary study outcome is the number of days alive out of hospital at 90 days post randomisation (DAOH-D 90). Participants who die on or prior to day 90 will be assigned zero days alive and out of hospital.

### 8.2 Secondary outcomes

1. All-cause mortality at 90 days
2. Time from randomisation until death (to day 90)
3. Days alive and at home at 90 days post-randomisation
4. Ventilator-free days to day 28
5. Vasopressor-free days to day 28
6. Renal replacement therapy-free days to day 28
7. Death or disability at 6 and 12 months\*

### 8.3 Tertiary outcomes

1. Incidence and duration of invasive mechanical ventilation
2. Incidence and duration of vasopressor support
3. Incidence and duration of acute renal replacement therapy
4. ED length of stay
5. ICU length of stay
6. Hospital length of stay
7. In hospital mortality (censored at 90 days)

8. Mortality at 6 and 12 months\*
9. Quality of life at 6 and 12 months\*
10. Cost-effectiveness measured as cost/QALY\*

\*May be reported separately when 12-month follow up complete

## 9. OVERALL STUDY DESIGN

### 9.1 Study design

The ARISE FLUIDS study is a multicentre, randomised, parallel group clinical trial of a restricted fluids and early vasopressor strategy compared to a larger initial IV fluid volume and later vasopressors for the haemodynamic resuscitation of patients with septic shock presenting to the ED. It will be conducted in hospitals in Australia and New Zealand with 1000 patients recruited over a 3-year period.

Each patient meeting all of the inclusion and none of the exclusion criteria will be randomised to receive haemodynamic resuscitation using either a restricted fluid and early vasopressor regimen (vasopressors arm) or a larger initial fluid resuscitation volume (fluids arm) followed by later introduction of vasopressors (if required). The intervention will be commenced in the ED and delivered for at least 6 hours, and up to 24 hours post-randomisation if admitted to the ICU or other critical care area where the study protocol can be faithfully delivered. Treatment will revert to usual care as determined by the treating clinician when the patient is transferred to a non-critical care ward. All enrolled participants will be followed up and assessed for the defined study outcomes.

Participants will be identified using a systematic approach to screening and assessment of patients with possible sepsis presenting to the ED in accordance with standard clinical practice.

### 9.2 Study population

Adult patients admitted to the ED of a participating institution with septic shock. Eligible patients must meet the inclusion criteria within the first 6 hours of ED presentation and must be randomised within 2 hours of meeting the last inclusion criterion.

### 9.3 Inclusion criteria

Patients will be eligible if ALL of the following criteria are met while in the ED:

1. Clinically suspected infection
2. Systolic blood pressure (SBP) <90 mm Hg or mean arterial pressure (MAP) <65 mm Hg, despite a  $\geq 1000$ ml cumulative total bolus of IV fluid administered over a maximum of 60 minutes; including pre-hospital boluses
3. Arterial or venous blood lactate >2.0 mmol/L
4. At least one dose of an IV antimicrobial has been commenced

## **9.4 Exclusion criteria**

Patients will be excluded if ANY of the following apply:

1. Age < 18 years
2. Confirmed or suspected pregnancy
3. Transferred from another acute care facility
4. Hypotension suspected to be due to a non-sepsis cause
5. >2L total IV fluid administered (including prehospital fluids but excluding drugs and flushes)
6. More than 6 hours has elapsed since presentation to the ED or more than 2 hours has elapsed since last inclusion criterion has been met
7. Treating clinician considers that one or both of the treatment regimens are not suitable for the patient or the study protocol cannot be delivered e.g. limitation of care, requirement for immediate surgery
8. Death is considered imminent or inevitable
9. Underlying disease that makes survival to 90 days unlikely
10. Inability to follow patient up to day-90 e.g. unstable accommodation, overseas visitor
11. Previously enrolled in this study

## **9.5 Screening Log**

All patients who meet all the inclusion criteria will be entered into the screening log. Those who are excluded will have all of their reason/s for exclusion recorded.

## **9.6 Co-enrolment**

Co-enrolment in another intervention trial evaluating haemodynamic resuscitation for septic shock is not permitted.

Co-enrolment in other interventional studies will be considered by the Management Committee as required.

# **10. STUDY PROCEDURES**

## **10.1 Randomisation**

Randomisation will be performed by the site investigator, research coordinator or delegated staff at each site. This will occur through a dedicated, secure, password-protected, encrypted website which is available 24 hours, 7 days a week. Patients will be randomised using computer-generated, block randomisation sequence with variable block sizes and stratified by participating centre. Patients will be assigned in a 1:1 ratio to either: the Vasopressors arm or Fluids arm. Upon randomisation, the website will assign a unique patient study number.

## 10.2 Study Treatment arms

All participants will have received a minimum of 1 L within 1 hour but not more than 2L of resuscitation fluids (including pre-hospital fluids) prior to randomisation. The study allocated treatment arm, either Vasopressors or Fluids, will run for at least 6 hours and up to a maximum of 24 hours post-randomisation whilst present in a critical care area (ED, ICU, HDU). After this time or discharge to a general ward area, whichever occurs first, care will revert to standard management as determined by the treating clinician. Choice of resuscitation fluids is at treating clinician discretion according to local practice.

Patient safety is paramount and at all times the precise timing and resuscitation targets will be at the discretion of the treating team.

## 10.3 Vasopressors arm

**A restricted fluids and early vasopressor strategy:**

**Cease IV fluid resuscitation.** If persisting hypotension and/or hypoperfusion **commence a vasopressor infusion** (e.g. noradrenaline) and titrate according to local practice to achieve target MAP. The target MAP will be determined by the treating clinician. Reassess at least hourly for up to 6 hours post-randomisation, **then as clinically required in conjunction with the protocol**. Boluses of **250ml** of IV fluids are permitted if deemed indicated by the treating clinician, including for the following reasons:

- Refractory hypotension
- Persistent hypoperfusion e.g. delayed capillary refill time
- Lactate >4 mmol/L and/or rising from previous level despite at least 2 hours of resuscitation
- Persistent tachycardia
- Oliguria <0.5 ml/kg/hr for at least 2 hours.

Maintenance fluids are strongly discouraged.

## 10.4 Fluids arm

**A larger initial intravenous fluid volume and later introduction of vasopressor strategy:**

**An fluid bolus of up to 1000ml will be administered over a maximum of 1 hour, if required, for persisting hypotension and/or hypoperfusion.** Reassess at least hourly to 6 hours post-randomisation, **then as clinically required in conjunction with the protocol**. Further IV fluid boluses of **500ml** are recommended as clinically indicated to achieve the target MAP. The target MAP will be determined by the treating clinician. Haemodynamic resuscitation will be guided by usual clinical assessment including vital signs, mentation, perfusion, and urine output until the treating clinician determines fluid resuscitation is no longer clinically required. **A minimum of**

**2-3 L (30 ml/kg)**, including pre-randomisation fluids, is recommended within 3 hours of ED arrival consistent with the SSC guidelines, unless clinically contraindicated [8]. Vasopressors may be commenced if blood pressure remains below target *despite* optimal fluid resuscitation as determined by the treating clinician.

If the patient is *in extremis*, vasopressors may be commenced concurrently with fluids. Maintenance fluids may be administered if indicated, in accordance with local practice.

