### **10.5.2 Monitoring for hypovolaemia or hypoperfusion**

Participants in both study arms will be **monitored for signs of hypovolaemia or hypoperfusion** and managed with additional IV fluids in accordance with the trial protocol. If a participant develops evidence of central (e.g. bowel) or peripheral (limb or digit) ischaemia or mottling, treat accordingly and continue the protocol where clinically appropriate. Signs of hypovolaemia or hypoperfusion may include persistent tachycardia, altered mentation, reduced capillary refill time and oliguria.

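### Two bedside instructions need reconciling: capillary refill time is given in opposite directions as a hypoperfusion sign (10.3 v 10.5.2), and the Fluids-arm 3-hour clock can run out before a permitted randomisation (10.4 v 9.4)

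*Protocol*

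**What the plan says.** **Volume and clock.** Section 10.4 recommends that Fluids-arm patients receive at least 2-3 L (30 ml/kg), "including pre-randomisation fluids, is recommended within 3 hours of ED arrival consistent with the SSC guidelines", with an exception for clinical contraindication.

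**Time of randomisation.** Section 9.2 says that patients "must meet the inclusion criteria within the first 6 hours of ED presentation and must be randomised within 2 hours of meeting" the last criterion. Exclusion 6 in Section 9.4 removes a patient once either limit has passed: "More than 6 hours has elapsed since presentation to the ED or more than 2 hours has elapsed since last inclusion criterion" was met.

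**Fluid on entry.** Section 10.2 says that every participant will have had at least 1 L "but not more than 2L of resuscitation fluids (including pre-hospital fluids) prior to randomisation". The same section states that "at all times the precise timing and resuscitation targets will be at the discretion of the treating team".

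**Capillary refill.** In the Vasopressors arm, Section 10.3 lists among the reasons for a fluid bolus: "Persistent hypoperfusion e.g. delayed capillary refill time". Section 10.5.2, which governs both arms, says that signs of hypovolaemia or hypoperfusion may include "persistent tachycardia, altered mentation, reduced capillary refill time and oliguria", and directs that such patients be managed with additional fluid within the protocol.

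**The concern.** Each conflict lies in text that staff act on, not in background.

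The volume recommendation is timed from ED arrival, whereas allocation can come hours later. If the deadline has passed when the patient is randomised, the arm's only numerical minimum volume gives the treating team no usable instruction. A monitor who reads it literally would record as missed something that allocation could never have achieved. The protocol relies on compliance monitoring to limit bias in an unblinded trial (10.10), and it reviews compliance and separation between arms after 150 participants (3.5.2 and 13.4).

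The capillary refill wording belongs to a safety-monitoring instruction. Two sections give the same measurement opposite meanings, so a site that follows one as written departs from the other.

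**Working it through.** **1. Capillary refill, side by side**

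| Section | Applies to | Refill time listed as the sign | Linked action |
|---|---|---|---|
| 10.3 | Vasopressors arm | delayed (longer) | 250 ml bolus permitted |
| 10.5.2 | both arms | reduced (shorter) | additional fluid under the protocol |

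A time cannot be both longer and shorter. For a Vasopressors-arm patient both sections apply at once. No arithmetic is needed; the conflict is in the wording.

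**2. The 3-hour clock**

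Inputs: deadline 3 h from ED arrival (10.4); latest randomisation 6 h from presentation (9.4, exclusion 6); fluid on entry 1 to 2 L (10.2); target 2 to 3 L (10.4). I treat ED arrival and ED presentation as the same moment.

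*Share of the permitted window after the deadline* = (6 - 3) / 6 = 3/6 = 50%. This is a share of hours, not of patients, because the protocol gives no distribution of randomisation times.

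*Shortfall at entry* = target minus volume already given:

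| Given before randomisation | Against 2 L | Against 3 L |
|---|---|---|
| 1 L | 2 - 1 = 1 L | 3 - 1 = 2 L |
| 2 L | 2 - 2 = 0 L | 3 - 2 = 1 L |

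So a patient who satisfies every entry rule can be randomised after hour 3 and still be 1 to 2 L short (entering with 1 L), or up to 1 L short (entering with 2 L). For that patient no fluid given under the allocation can arrive before the deadline. Section 10.4 supplies no second clock.

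*Illustration for patients randomised before hour 3.* Assume fluid runs at 1 L per hour after allocation. The latest randomisation that still meets the deadline is 3 h minus the shortfall in litres:

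- 1 L on entry, 2 L target: 3 - 1 = 2 h
- 1 L on entry, 3 L target: 3 - 2 = 1 h
- 2 L on entry, 3 L target: 3 - 1 = 2 h

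The rate is borrowed from the first bolus in 10.4 (up to 1000 ml in at most an hour). Faster delivery is allowed, and no rate is given for later boluses, so these times are indicative only. The result for patients randomised after hour 3 does not depend on any rate.

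**3. Effect on the trial's numbers**

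None. The sample size in 13.1 uses neither the volume target nor the clock.

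**The case against.** The strongest reply is that the volume minimum is only recommended, has a contraindication exception, and sits under the Section 10.2 clause that leaves timing and targets to the treating team. That stands: no mandatory rule is broken, and a patient who already has the volume is unaffected. But discretion does not supply a clock where the stated one has expired.

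On capillary refill, the reply is that the wording in 10.5.2 is a drafting slip in a list of possible signs, and that clinicians decide throughout. That may be so, and it limits the harm. It does not remove the conflict from a safety instruction.

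A reader might infer four stronger things, none of which the documents support:

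- *Bias towards no difference.* The arm-specific instructions run from randomisation whether or not the 3-hour target still applies. The Fluids arm allows a first bolus of up to 1000 ml, then 500 ml boluses, and maintenance fluid. The Vasopressors arm stops fluid resuscitation, allows 250 ml boluses and discourages maintenance fluid. The target is a minimum, not a cap, so loss of separation is not shown.
- *Enrolment up to 8 hours.* Section 9.2 read alone suggests 6 + 2 = 8 h. Section 9.1 requires that no exclusion criterion is met, and exclusion 6 stops enrolment at 6 h.
- *Litres contradicting ml/kg.* The two agree from 2000/30 = 66.7 kg to 3000/30 = 100 kg, and Section 6 presents the litres as the equivalent for a typical adult. This is a rounded gloss, not an error.
- *Adherence that cannot be judged.* Fluid volumes before and after randomisation and vasopressor times are all collected (12.2), and nothing ties the 150-participant review to the 3-hour clock.

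**Conclusion.** The point holds as two wording conflicts in operative instructions, at minor severity.

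First, Sections 10.3 and 10.5.2 give capillary refill time in opposite directions. This rests on the text alone.

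Second, Section 10.4 sets a deadline that lawful enrolment can overrun. Three of the 6 permitted hours fall after it, and a late entrant can be up to 2 L short against the upper figure. This assumes that ED arrival and ED presentation are the same moment and that exclusion 6 governs. How many patients are affected is unknown and could be small if most are randomised early. No bias, power loss or change in sample size is claimed.

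**What to change.** Reconcile Section 10.5.2 with 10.3, so that capillary refill time is described in one direction throughout. Reconcile 10.4 with 9.2, 9.4 and 10.2, so that the protocol states what the volume recommendation means for a Fluids-arm patient who is randomised after its deadline and is still short of the volume. Align the time limit in 9.2 with exclusion 6 in the same edit. Which sign, clock or volume applies is a clinical decision for the sponsor; none is proposed here.

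Optionally, the 150-participant review could express fluid volume and time to vasopressor from randomisation, which is defined for every participant in both arms. That corrects no stated error.

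Cost: amendment wording and a short training note to sites. No new data are needed.
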